### Sample size and feasibility

Based on our previous findings, the expected diabetes risk reduction based on previous face to face prevention studies has been shown to be 28–32%. We hypothesized that a digital intervention would enable a 24% reduction in the incidence of T2D (*p* < 0.05) compared to the control group. The effect size selected was based on published literature which suggests lower effectiveness for digital compared to face-face interventions.

To demonstrate that difference as significant at *p* < 0.05 and with 80% power and accounting for approximately 20% drop-out rate, 3,240 participants will be recruited.

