### Primary and secondary outcomes

The primary outcome is incidence of T2D at 24 months (as determined by the specific criterion applied to each individual on their admission into the study (fasting glucose, 2-hour glucose on OGTT, and/or HbA1c). For example, if an individual’s prediabetes status was defined by HbA1c value (within the range 42-47mmol/mol), their progression to type 2 diabetes will be defined by the associated HbA1c threshold (48mmol/mol or greater). Changes over 6 and 12 months are considered secondary outcomes.

Secondary outcomes are listed in Table 1 and include changes in cardiometabolic outcomes; intervention uptake, use and satisfaction; behavioural and clinical outcomes; and costs related to implementation. Data will be collected at baseline, and 6, 12 and 24 months as outlined in Table 1.

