### Statistics and data analysis

The primary analyses will be based on an intention to treat (ITT) principle. All participants who are randomised into the study will be included in the ITT analysis and the analysis is conducted according to the randomised treatment arm. Outcomes will be assessed for normal distribution.

For the primary outcome, the incidence of T2D in each study arm will be determined based on the participants’ entry criterion. Change in HbA1c, fasting glucose, or 2-hour OGTT glucose values will be calculated from baseline to endpoint (at 12 months and 24months) and reported based on the specific criterion applied to each individual on their admission into the study. Outcomes will be assessed by two-tailed unpaired t-test if normally distributed or the Wilcoxon Rank sum test if non-normally distributed.

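### The primary outcome is binary, but the only inference named is a t-test or Wilcoxon test on independent participants; no fitting method tests the 24% reduction or puts an interval on it

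*Protocol article*

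**What the plan says.** All places are in the protocol article.

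- **Primary and secondary outcomes.** "The primary outcome is incidence of T2D at 24 months". It is reached by crossing a diagnostic cut-off on the criterion by which the participant entered. For someone admitted on HbA1c, "their progression to type 2 diabetes will be defined by the associated HbA1c threshold (48mmol/mol or greater"). Each participant therefore ends as a yes or a no.
- **Sample size and feasibility.** "We hypothesized that a digital intervention would enable a 24% reduction in the incidence of T2D" relative to control. The aim is then put as a significance statement: "To demonstrate that difference as significant at *p* < 0.05". Power is set at 80%, dropout is taken as about 20%, and the total is 3,240.
- **Participant recruitment and cluster randomisation, and Fig. 2 legend.** Clusters are allocated 1:1. There are 60 in Tamil Nadu and 30 in Delhi, with 36 participants each.
- **Statistics and data analysis.** Analysis is by intention to treat, and outcomes are to be checked for normality. The second paragraph opens with the primary outcome and says that incidence will be established in each arm. It then turns to changes in HbA1c, fasting glucose or 2-hour glucose at 12 and 24 months. It ends: "Outcomes will be assessed by two-tailed unpaired t-test if normally distributed or the Wilcoxon Rank sum test", the latter if the data are not normal.

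The article names no test of proportions, risk ratio, odds ratio, binary regression model or confidence interval, and no method that allows for clusters.

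**The concern.** The last sentence of the statistics section speaks of outcomes without qualification and stands in the paragraph that begins with the primary outcome. Read literally, it covers a 0/1 variable. Checking such a variable for normality has no meaning, and the non-normal branch leads to a rank-sum test, whose usual output is a p-value rather than a risk ratio with an interval. The sample size, however, rests on a reduction in incidence, so the reader will want that reduction with its uncertainty.

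The same sentence has a second defect. The unpaired t-test and the rank-sum test both take participants as independent, whereas the unit randomised is a ward, a block group or a group of villages. An analyst who followed the text would report standard errors that are too small whenever outcomes correlate within clusters.

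So two things are at stake: whether the primary result comes with a fitting effect measure and interval, and whether its p-value keeps the stated 5% level.

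**Working it through.** **Inputs from the article.** N = 3,240; about 20% dropout; 1:1 allocation; 24% reduction, read as relative because it is set beside a risk reduction of 28–32% in face-to-face studies, so RR = 0.76; two-sided 5%; 80% power; 90 clusters of 36.

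**Assumptions.** The article gives neither a control-arm incidence nor an intracluster correlation (ICC). I use control incidences of 15%, 20% and 30% and ICCs of 0.01, 0.02 and 0.05 for illustration only.

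**1. The plan's own figure.** The cluster counts agree with the total: (60 + 30) × 36 = 3,240. The power calculation cannot be reproduced because the control incidence is not given. Solving backwards with the two-proportion formula, RR 0.76 and 20% dropout, 3,240 corresponds to a control incidence of about 15–17% without clustering, 19–21% at ICC 0.01, 22–26% at 0.02 and 31–36% at 0.05. The size is compatible with a binary endpoint but cannot be verified.

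**2. Analysable number.** 3,240 / 2 × 0.8 = 1,296 per arm.

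**3. Does the wrong type of test change the p-value?** The tests were run on 0/1 data with 1,296 per arm, clusters ignored:

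| Events, control vs intervention | t-test | Wilcoxon | Chi-square |
|---|---|---|---|
| 259 vs 220 | 0.0484 | 0.0485 | 0.0484 |
| 194 vs 165 | 0.0992 | 0.0992 | 0.0991 |

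It hardly does. The mismatch affects the effect measure and its interval, not the unclustered p-value.

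**4. The interval that is not specified.** RR = b/a, where a and b are the control and intervention event counts; SE(log RR) = √(1/a − 1/n + 1/b − 1/n) with n = 1,296; limits = RR × exp(±1.96 SE). With events chosen to give RR close to 0.76 and clusters ignored:

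| Assumed control incidence | Events | RR (95% CI) | Risk difference |
|---|---|---|---|
| 15% | 194 vs 148 | 0.76 (0.62–0.93) | 46/1,296 = 3.5 points |
| 20% | 259 vs 197 | 0.76 (0.64–0.90) | 62/1,296 = 4.8 points |
| 30% | 389 vs 295 | 0.76 (0.67–0.86) | 94/1,296 = 7.3 points |

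**5. What clustering does.** Design effect = 1 + (m − 1) × ICC, with m = 28.8 (36 × 0.8) or 36. The true error rate of a nominal 5% test is about 2 × [1 − Φ(1.96/√design effect)].

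| Assumed ICC | Design effect (m = 28.8; 36) | True error rate |
|---|---|---|
| 0.01 | 1.278; 1.35 | 8.3%; 9.2% |
| 0.02 | 1.556; 1.70 | 11.6%; 13.3% |
| 0.05 | 2.39; 2.75 | 20.5%; 23.7% |

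On the log scale the interval widens by √(design effect). For 259 vs 197 events and m = 28.8, 0.64–0.90 becomes 0.63–0.92 at ICC 0.01, 0.62–0.94 at 0.02 and 0.59–0.99 at 0.05. For the borderline 259 vs 220, z = 1.974. At ICC 0.02, z = 1.974/√1.556 = 1.58, so p moves from 0.048 to about 0.11.

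**The case against.** The strongest reply is that the test sentence directly follows the continuous changes in HbA1c and glucose, which those tests suit. On that reading the primary outcome is not sent to a rank test; the article simply names no test for it, and a condensed article may leave that to a fuller document. This is a fair possibility, and it rules out saying with certainty that the primary endpoint will be analysed by Wilcoxon. It does not clear the text. The sentence is unqualified and stands in the paragraph on the primary outcome, so a method is stated whose scope is left open. On either reading, the tests it names ignore the randomised clusters.

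A reader might also infer that the trial cannot estimate the 24% reduction. The article does not support that. Incidence will be obtained in each arm, so a crude ratio and difference follow at once, and the data to be collected allow a proper analysis. A t-test on 0/1 data even gives a risk difference with an interval, although one that ignores clusters. The p-values in step 3 show that the mismatch alone would not distort an unclustered test.

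Nor does the article say that normality will be judged by a formal test. A graphical check fits the wording equally well, so an argument that large samples would reject trivial departures is conjecture and forms no part of this point.

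**Conclusion.** The point holds in a limited form. The endpoint is binary and the hypothesis concerns incidence, yet the only stated inference is made for continuous or ordinal data on independent participants. A crude ratio is available; what is missing is a stated method that suits a binary endpoint and a cluster design, to test the reduction and to put an interval on it.

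The loss from the type of test is one of effect measure and interval. The numerical harm comes from ignoring clusters: error rates of roughly 8% to 24% over assumed ICCs of 0.01 to 0.05. Those rates and the illustrative intervals rest on assumed ICCs and control incidences. The mismatch between endpoint, design and named tests does not; it follows from the text alone. Because it touches the primary hypothesis, it should be settled before outcome data are analysed.

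**What to change.** 1. State the primary analysis as the 24-month risk ratio, with the risk difference, each with a 95% confidence interval, from a binary model that accounts for cluster. A modified-Poisson GEE, or a mixed logistic model with marginal standardisation, would serve.
2. Take the primary outcome out of the normality check and the t-test/Wilcoxon sentence, and say which outcomes that sentence was meant for.
3. Analyse continuous outcomes, including the glycaemic changes, with a cluster-aware linear model instead of the two independent-sample tests.

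Adjustment for baseline HbA1c or glucose is optional and not part of the error.

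The cost is analysis wording only: no change to recruitment, visits or data collection. The ethics section says that recruitment is still under way, so the wording can be corrected in time. If a fuller protocol or analysis plan already specifies such a model, it is enough to bring the article's sentence into line with it.

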## Discussion

This study is the largest study to assess the effectiveness of a digital app intervention for the prevention of T2D in India to date. The adoption of digital tools for health behaviour modification offers a scalable and potentially cost-effective approach, particularly in settings with limited healthcare resources. However, realising their full potential, requires addressing several challenges.

A key challenge is the variation in digital literacy and varying levels of access to smartphone technology, particularly in rural populations. Rural India has experienced rapid internet adoption, driven by the surge in online services such as digital payments, e-learning, and telemedicine during the COVID-19 pandemic. With more than 821 million users, rural India has more internet users than urban India [24]. The Indian government’s Digital India Program has also played a crucial role in not only promoting digital literacy, but also providing infrastructure in rural areas [25]. Despite this, disparity in internet access across India poses another significant barrier, and although internet penetration is increasing, many rural areas still experience inconsistent connectivity. To mitigate this, low-data usage was incorporated into the design of the app. Furthermore, the app is designed to accommodate diversity, offering content in three languages with dietary and lifestyle information tailored to the local population. Language-agnostic features, such as gaming elements, further enhance accessibility, making the app more inclusive for users with varying literacy levels.

Identifying and reaching individuals at high risk can be challenging, particularly in rural areas [26]. The protocol includes proactive strategies to engage these populations effectively. Cluster randomisation was employed in rural areas to prevent cross-contamination between groups, as close-knit communities may increase the risk of intervention overlap [27].

Another key factor in determining the success of the intervention is user adherence and engagement with the app. The study intervention offers a personalised approach to enhance individual engagement through gamification and motivation strategies, such as challenges, rewards, and progress tracking. By offering a more interactive experience, the app encourages sustained participation and adherence to healthy lifestyle changes, which are necessary for T2D prevention [23]. App data usage will be used to assess uptake with the digital intervention.

Finally, due to the high prevalence of anaemia in the South Asian population, which can affect HbA1c readings and lead to inaccurate assessments of diabetes risk [21, 22], recruitment is not based solely on HbA1c levels. This dual approach ensures more accurate identification of high-risk individuals. Another challenge in conducting studies in rural settings is the difficulty of using venous sampling and transporting blood samples to centralised laboratories, particularly due to limited infrastructure, logistical constraints and time taken. To address this, the study utilises capillary OGTT for more practical and immediate results in the field [28].

In conclusion, despite the challenges, the use of a digital platform reduces the need for extensive physical infrastructure and human resources, offering a scalable solution that could be highly cost-effective in resource-constrained environments. If proven successful, the study has the potential to contribute to the growing body of evidence supporting digital health solutions for diabetes prevention, with broader implications for public health policy and healthcare delivery in resource-constrained settings.

## Data Availability

No datasets were generated or analysed during the current study.
